## Background

### Current knowledge and practice

OHCA carries a high mortality rate, with 30-day survival rate of 14% in Norway ^4^. For non-traumatic cardiac arrest, the most frequent aetiology is a cardiac disease ^5,6^. Cardiopulmonary resuscitation (CPR) prolongs the time prior to hypoxic irreversible damage, by delivery of partially oxygenated blood to vital organs ^7^. The brain is sensitive to hypoxia and the high mortality rate after the patients are admitted to hospital is primarily caused by anoxic brain damage ^8^.

The treatment of out-of-hospital cardiac arrest are advanced cardiovascular life support (ACLS) as stated in the guidelines from the Norwegian Resuscitation Council ^9^ and the European Resuscitation Guidelines ^10^ (Figure 1).

[figure not shown]

*Figure 1. Guidelines from the European Resuscitation Council*

### Other adjuncts to advanced cardiovascular life support

Other interventions such as fibrinolysis or percutaneous coronary intervention (PCI) are well documented therapies and recommended as appropriate ^10^. Extracorporeal membrane oxygenation (ECMO) is a possible intervention in the cardiac arrest setting ^11^. This is currently not recommended in the guidelines from the Norwegian Resuscitation Council but is in use in some centres. Some study centres, for instance Oslo University Hospital, may have an extracorporeal-CPR (E-CPR) protocol in place. Another future intervention is the selective aortic arch perfusion technique, in which oxygenated blood is injected into the aorta under pressure, through a special designed catheter ^12,13^. This technique has yet to be tested in patients.

### Rationale for use and anticipated clinical benefits of REBOA

REBOA is a technique used to provide occlusion of the aorta by inflation of an intra-aortic balloon. REBOA can be used in management of haemorrhagic shock or cardiac arrest secondary to trauma. Recently, REBOA has been proposed as an adjunct treatment in management of non-traumatic cardiac arrest patients ^14,15^. Thoracic aortic occlusion provides a redistribution of the cardiac output to organs proximal to the occlusion through reduction of vascular volume where generated cardiac output is distributed. Preclinical studies demonstrate that REBOA during cardiopulmonary resuscitation provide both increased coronary artery blood flow and perfusion pressure and increased rates of return of spontaneous circulation (ROSC) ^12,13,16–21^. The coronary perfusion pressure is the driving force of blood through the coronary arteries, calculated as the diastolic aortic pressure minus the pressure in the right atrium. Hence, increased aortic diastolic blood pressure will increase the coronary perfusion pressure. This is shown to be associated with ROSC in humans ^22^. REBOA during experimental resuscitation also increase blood flow to the carotid arteries ^19,23^, cerebral arteries ^17,18,23–25^ and cerebral perfusion pressure ^17,18,23,26^. These findings support our hypothesis that patients with non-traumatic cardiac arrest might benefit from REBOA during resuscitation. A few published case reports demonstrates the effect of REBOA on humans ^27–30^. Currently, only one study reports the prospective use of REBOA in clinical use ^1^. This pilot trial demonstrated that pre-hospital REBOA procedure during resuscitation is feasible and did not negatively influence the quality of the ACLS.

We anticipate that the intervention will provide an improvement in both systolic and diastolic blood pressure. This could potentially improve perfusion of the brain and heart during CPR. Brain tissue is highly sensitive to hypoxemia and improved systolic blood pressure, with possible improved perfusion of the brain, is likely beneficial. The potential clinical benefit in this trial is therefore increased rate of ROSC and survival to hospital, possibly also improved 30-day survival rate.

Besides the potential benefit of REBOA for cerebral and coronary circulation during CPR, insertion of the catheter may have some other advantages in the post-ROSC phase. The CHEER trial demonstrated that patients can survive with good neurological outcomes after more than 30 min of pre-hospital resuscitation if they were given circulatory support in the form of extracorporeal membrane oxygenation (ECMO) and definitive intervention in hospital ^31^. The introducer sheath in the femoral artery used to establish REBOA can be used for quick access to ECMO or other endovascular interventions such as PCI, directly after admission.

### Epidemiology of cardiac arrest

The number of out-of-hospital cardiac arrest in Norway was 3 172 in 2017, which correlates to an incidence of 60/100 000 inhabitants per year, increasing from 53/100 000 in 2015 ^4^. Many patients with OHCA have little comorbidity and a potential for good long-term function ^32^. A needs assessment based on the Norwegian Cardiac Arrest Registry show that 240 OHCA patients each year in Norway could be eligible for the REBOA procedure ^33^. This needs assessment analysis is based on a national data set. However, many European countries have a similar population pattern, and many have similar physician-staffed emergency medical services (P-EMS). The results of this needs assessment are therefore likely transferable to other Nordic countries. In countries with more dense population, more patients could be eligible for the REBOA procedure due to shorter P-EMS response intervals.

## Study Rationale

The purpose of the study is to assess the efficacy of REBOA as an adjunct treatment to ACLS in non-traumatic cardiac arrest and the effects of this intervention on ROSC. This is not a trial to test any medical device, nor to compare the effect of different REBOA catheters.

The use of REBOA during cardiopulmonary resuscitation is a novel procedure, which is only prospectively investigated in one published study ^1^. The procedure is researched in preclinical setting and animal models ^12,13,16–21,23–26^, however, only a few case reports are published on the effect in humans ^27–30^. This trial will therefore fill a knowledge gap. The survival rate after OHCA is dismal and a large part of these patients have small comorbidity burden ^32^. A possible beneficial intervention might therefore improve both survival rate and quality of life in the survivors. This trial will be important to obtain new knowledge for health services globally. If the hypothesis is correct and REBOA improves survival and/or cerebral status of the survivors, the trial can contribute to initiate further research that improve the current best practice.

## Academic study

This study is not part of an application for regulatory approval of medical devices. It is not conducted to establish or verify the clinical benefits of a device as specified by its manufacturer. All catheters used for balloon inflation of the aorta is CE marked and are used within their regulatory approval. No device manufacturer is involved in the design of this trial, nor will any manufacturer have access to data or results other than those in the public domain. The sponsor retain ownership of all data and results generated through this trial. It is not designed to report to any Notified Body to alter CE-markings or CE-approvals or other regulatory applications for medical devices.

# Objectives and endpoints

## Primary objective of the study

The primary objective is to assess the efficacy of REBOA as an adjunct treatment to advanced cardiovascular life support in patients with out-of-hospital cardiac arrest, measured as primary endpoint: return of spontaneous circulation.

## Secondary objective of the study

Secondary objectives of this trial are to describe the hemodynamic physiology of aortic occlusion during ACLS and a description of any adverse events and 30 days survival with good neurological status.

## The primary endpoint

The primary endpoint of this study is the proportion of patients that achieve return of spontaneous circulation (ROSC) with a duration of at least 20 minutes, i.e. sustained ROSC.

This clinical endpoint is based on the following Utstein definition updated in 2019 ^34^: *“Sustained ROSC is deemed to have occurred when chest compressions are not required for 20 consecutive minutes and signs of circulation persist.*”

Whether or not a patient has obtained ROSC is a comprehensive clinical assessment performed at regular intervals during the provision of CPR. This assessment is made in patients with an organized rhythm on ECG during pauses in chest compressions. ROSC should be suspected if one or more of the following occur ^34^:
•    Signs of life, including coughing, movement and/or regular breathing
•    Palpable pulses in radial, carotid and/or femoral arteries
•    Invasive systolic blood pressure > 50 mmHg

The current 2015 guidelines from the European Resuscitation Council state that a rise in measured end-tidal CO2 values (EtCO2) during CPR is indicative of ROSC ^10^. Establishment of REBOA may also give a transient increase in EtCO2 ^1^. There are no current cut-off values for EtCO2 deemed appropriate to use in this setting to indicate whether ROSC has occurred or not. Any rise in EtCO2 should be clinically assessed in conjunction with other signs of circulation.

If the patient has shorter periods of ROSC and do not obtain a persisting circulation, the patient has not met the primary endpoint. In the documentation, ‘any ROSC’, should be stated in these instances.

## The secondary endpoints

1. 30-day survival rate with good neurologic status defined as modified Rankin scale (mRS) score 0-3.

We dichotomise the mRs into good (score 0-3) and poor (score 4-6) neurological state (appendix 29.2) to enable both binary statistical analysis and a reasonable clinical interpretation of trial results, as performed in other large cardiac arrest studies ^35^. The mRS is commonly used as a primary outcome scale for acute stroke trials ^36^, but is increasingly used also in cardiac arrest research and has been recommended in the International Liaison Committee on Resuscitation as part of the Utstein template ^37,38^. The outcome is also in accordance with recently published Core Outcome Set for Cardiac Arrest trials ^39^.

1. Difference in end-tidal CO2 measurements in the control group and the intervention group after aortic occlusion.

EtCO2 measurements is a proxy measurement of central circulation, shown feasible in this setting ^1^. This pilot study reported a significant increase in EtCO2 after 30, 60 and 90 seconds. This allows for comparison of the two groups, with a possible increase in central circulation as a hypothesized reason to an increased proportion of patients achieving ROSC. In the control group, EtCO2 is measured after airway management is completed. In the intervention group, EtCO2 is measured before balloon inflation and 30, 60 and 90 seconds after balloon inflation.

1. Change in blood pressures after aortic occlusion.

In the intervention group, intra-aortic blood pressure measurements from the REBOA catheter are recorded. This apply only to the catheters with CE/FDA approval for invasive blood pressure measurements and will therefore be assessed in a sub-group of the participants. Continuous registration of invasive blood pressure will start before aortic occlusion.

1. Left ventricular ejection fraction (LVEF) measured by echocardiography

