### During Treatment

**Outline of a REBOA procedure at an out-of-hospital cardiac arrest**

The ambulance personnel and the P-EMS crew establish ACLS as per national guideline at site. Either manual compressions or a mechanical chest compression is used. Airway management is handled by either endotracheal intubation or a supraglottic airway device. Intravenous or intraosseous access on the upper body is established. Cerebral oximetry is used, if available. If the patient is eligible for inclusion, the patient is randomised by that the physician opens the next numbered sealed envelope from the REBOA equipment. The randomisation procedure is described in section 10.1.

The paramedic prepares the REBOA-equipment, while the physician prepares the ultrasound machine and examines the patient for visible femoral vessels. Most physicians are right-handed and therefore will prefer to cannulate the patient’s right femoral artery, while placed on the patient’s right side. The paramedic prepares the equipment at the patient’s foot. The femoral inguinal area is washed with antiseptic and a sterile drape covers the patient, from abdomen to distal.

Arterial cannulation is performed ultrasound guided, with out-of-plane technique (Figure 4).

[figure not shown]

*Figure 4. Ultrasound guided femoral arterial cannulation*

After the femoral artery and vein is identified, the artery is cannulated with a 19 G needle and a flexible guidewire is inserted 60 cm. The cannulation can be performed in the ventilation phase of CPR or a 10-20 second pause in chest compression is allowed for. This hands-off time is considered common practice. After the guidewire is placed, the needle is removed, and ultrasound images of the guidewire position is obtained and stored. A scalpel is used to make a small incision next to the guidewire, to widen the entrance point. A 7 Fr introducer sheath is inserted over the guidewire and the stylet is removed (Figure 5).

[figure not shown]

*Figure 5. Insertion of introducer in femoral artery*

If the catheter in use is the ER-REBOA catheter, the guidewire is also removed, and the balloon sheath is placed. If the catheter is the REBOA Medical balloon, the guidewire will remain and the catheter is placed over the guidewire, through the introducer. The balloon sheath is inserted 50 cm for a Zone 1 aortic occlusion (Figure 6) ^49^, by use of measure marks on the catheter. Zone 1 is favoured for best haemodynamic effect ^49,50^.

[figure not shown]

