## Data collection during study period

Data will be registered according to this schedule.

[figure not shown]

These data points will be registered:

| **All patients** - data reported after randomisation | |
| --- | --- |
| Age |  |
| Gender |  |
| Habitus | *Cachectic, Normal, Adipose* |
| Location of the incident | *Public outdoors, public indoors, private indoors* |
| All concomitant medication and dose used |  |
| Route of administration | *Intravenous, intraosseous* |
| All relevant times | *DD.MM.YYYY: hh:mm* |
| Time of dispatch |  |
| Time of arrival |  |
| Time of randomisation |  |
| Cardiac rhythm at randomisation and fluctuations in rhythm during resuscitation | *VF, VT, PEA, AS* |
| Suspected aetiology of arrest | *cardiac, respiratory, intoxication/poisoning, non-traumatic haemorrhage* |
| Number of defibrillations | *n* |
| Compression machine used | *yes/no* |
| Airway management (main method) | *Supraglottic airway, Endotracheal intubation* |
| ROSC more than 20 minutes | *yes/no* |
| Data file from monitor used |  |

| **Control group - additional data** | |
| --- | --- |
| End-tidal CO2 measures after randomisation and after ROSC | *kPa* |
| Other relevant times | *DD.MM.YYYY hh:mm* |
| Time of ROSC |  |
| Time of departure from scene |  |
| Time of admission to hospital |  |

| **REBOA group - additional data** | |
| --- | --- |
| Space to perform procedure | *Good/acceptable, Challenging, Impossible* |
| Visibility/light conditions | *Good/acceptable, Challenging, Impossible* |
| Temperature | *Good/acceptable, Challenging, Impossible* |
| Wind/rain conditions | *Good/acceptable, Challenging, Impossible* |
| Available resources on the scene that were used | *Bystanders, Another doctor, Ambulance, Fire brigade* |
| Ultrasound image obtaining | *Good/acceptable, Challenging, Impossible* |
| Data file from ultrasound machine |  |
| Cannulation site | *Left, Right* |
| Numbers of cannulation attempts | *n* |
| End-tidal measures | *kPa* |
| Before and after inflation of balloon, and after ROSC |  |
| Palpable pulse in left radial artery | *yes/no* |
| before balloon inflation |  |
| after balloon inflation |  |
| Other relevant times | *DD.MM.YYYY hh:mm* |
| Time of balloon occlusion |  |
| Time of ROSC and deflation of the balloon |  |
| Time of departure from scene |  |
| Time of admission to hospital |  |

| **Delivered to hospital - additional data** | |
| --- | --- |
| Blood gas from admission |  |
| pH |  |
| pCO2 | *kPa* |

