## Procedures for data review and editing

After randomisation each patient will be given a unique study number. The site investigator or designee will handle an enrolment log (*Subject ID log* and *Screening log*, appendix 29.7 and 29.8) which include the patients name, date of birth and study number. Subsequent data will be identified only by the study number. No identifiable data will be entered to the CRF. The enrolment log will be stored separately at each study site.

Data that are not uploaded to the CRF will be handled by the site investigator only. The SI is responsible for an interview of the involved personnel, to gather the necessary data and to edit and upload this to the secure database and entry into the CRF. The data file from the monitor used in all randomised patients, and the ultrasound images from the patients in the intervention group, are preserved and protected in the REBOARREST data space in HUNT Cloud. Data integrity policies and data integrity controls are to ensure that investigators cannot remove raw data, and that duplicate copies can be made available for accountability audits.

If an investigator for some reason must withdraw from the study, his/her responsibility is transferred from this investigator to the site investigator and the project management, which will make efforts to appoint a new investigator, if necessary.

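### The between-group EtCO2 endpoint sets REBOA values timed from balloon inflation against control values with no corresponding time, so treatment is mixed with elapsed CPR time and post-randomisation selection

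*Protocol*

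**What the plan says.** Protocol section 6.4 lists as a secondary endpoint: "Difference in end-tidal CO2 measurements in the control group and the intervention group after aortic occlusion". It presents EtCO2 as a proxy for central circulation and as a possible explanation for more ROSC, and says the measurements permit a comparison of the two groups.

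The measurement times differ by arm:

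- Control, section 6.4: "In the control group, EtCO2 is measured after airway management is completed".
- REBOA, section 6.4: "In the intervention group, EtCO2 is measured before balloon inflation and 30, 60 and 90 seconds after balloon inflation".
- Control, data table in section 12.2: "End-tidal CO2 measures after randomisation and after ROSC".
- REBOA, same table: "Before and after inflation of balloon, and after ROSC".

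Section 9.5 says that EtCO2 will be analysed by regression. It also accepts that some REBOA patients may reach ROSC, be declared dead or have the procedure aborted before the aorta is occluded. Section 12.3 provides for storage of a further source: "The data file from the monitor used in all randomised patients". The protocol does not link that file to the EtCO2 endpoint.

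**The concern.** A randomised comparison of a physiological measure needs the two arms measured at comparable times and in comparable patients. Here the clock in one arm starts at an event that the other arm never has, and no substitute time is set for controls.

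Two things follow. If EtCO2 changes as resuscitation goes on, a difference in elapsed CPR time appears as a difference between treatments. If patients who leave before inflation differ in EtCO2 from those who stay, the REBOA values come from a selected subset while the control values need not. The second is plausible on the protocol's own account, because section 6.3 notes that a rise in EtCO2 points to ROSC, so early ROSC and EtCO2 are likely to be related.

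At stake is the reading of the mechanism. Among the secondary endpoints in section 6.4, blood pressure is recorded in the REBOA arm only and with certain catheters only, and ejection fraction is given no timing relative to occlusion. EtCO2 is the one between-group endpoint aimed at circulation after occlusion.

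**Working it through.** **Step 1: order of events (section 11.1.2).** ACLS is established first. As part of it, "Airway management is handled by either endotracheal intubation or a supraglottic airway device". The envelope is opened next. In the REBOA arm, ultrasound, femoral cannulation, guidewire, sheath and catheter placement then precede inflation.

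| Arm | Stated time of EtCO2 | Position in the sequence |
|---|---|---|
| Control (6.4) | after airway management | open-ended; its starting point precedes randomisation |
| Control (12.2) | after randomisation, and after ROSC | open-ended; its starting point precedes inflation |
| REBOA (6.4, 12.2) | before and after inflation (30, 60, 90 s), and after ROSC | after the whole cannulation procedure |

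No row gives controls a time that corresponds to inflation or to 30, 60 or 90 seconds after it.

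**Step 2: who contributes.** By section 9.5, REBOA patients can reach ROSC, die or have the procedure aborted before occlusion. They cannot have a post-inflation value. A control who reaches ROSC or dies equally early can have a value after airway management or after randomisation. Analysis by randomised group cannot restore values that never existed.

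**Step 3: how large the bias could be.** The protocol gives no figure for this endpoint to reproduce: no SD, no change of EtCO2 over time, no delay to inflation and no share leaving before occlusion. Everything below except the 100 patients per arm (section 9.2) is an assumption, with no treatment effect built in:

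- EtCO2 at randomisation has mean 4 and SD 1.5 kPa, and the control value is taken then;
- drift b is between -0.05 and +0.05 kPa/min, and the delay d to inflation is 5 to 15 min;
- a share q of 0 to 20% of the REBOA arm leaves before occlusion, weighted towards higher EtCO2 (probability proportional to exp(0.8 × standardised value), capped at 1).

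*Drift alone.* False difference = b × d. SE = 1.5 × √(1/100 + 1/100) = 0.212 kPa. The chance of a two-sided p below 0.05 is 1 - Φ(1.96 - |diff|/SE) + Φ(-1.96 - |diff|/SE).

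- 0.05 × 5 = 0.25 kPa: 22%.
- 0.05 × 10 = 0.50 kPa: 65%.
- 0.05 × 15 = 0.75 kPa: 94%.

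*Selection alone.* Before the cap, leavers average 0.8 × 1.5 = 1.2 kPa above the mean, so those remaining lie q × 1.2/(1 - q) below it.

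- q = 10%: 0.1 × 1.2/0.9 = 0.13 kPa below; simulated -0.13 kPa, false-positive rate 9%.
- q = 20%: 0.2 × 1.2/0.8 = 0.30 kPa below; simulated -0.28 kPa with the cap, false-positive rate 24%.

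*Both together.* The most negative case (d = 15, b = -0.05, q = 20%) gives -1.03 kPa and a false-positive rate above 99%. The most positive (d = 15, b = +0.05, q = 0) gives +0.75 kPa. The two can also nearly cancel: d = 5, b = +0.05, q = 20% gives -0.035 kPa and 5%. With no drift and no selection the difference is 0 and the rate is 5%.

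These runs show that the bias can be large, can be absent and can take either sign. They do not estimate it. If leavers were mainly patients dying with low EtCO2, the selection term would change sign.

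**The case against.** The strongest reply is that the protocol leaves the control time open rather than fixing it wrongly, and that time alignment, analysis sets and handling of early ROSC belong in the separate SAP promised in section 9. That SAP is not at hand and may settle all of this. The reply stands for the analysis detail. It does not remove the point, because section 6.4 itself sets the measurement schedule, and values collected on that schedule cannot be aligned by regression afterwards.

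Four stronger readings are tempting but not supported:

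- *Control values are fixed early, at airway completion or randomisation.* Both sections set only a lower bound. The control time is unmatched; it is not shown to be early, and no lag in minutes can be read from the documents.
- *No control value exists at a comparable time.* Monitor files are kept for all randomised patients and may hold one. The protocol does not say what they record or that the endpoint uses them.
- *Sections 6.4 and 12.2 contradict each other.* In the described sequence a value taken after randomisation is also after airway management, so 12.2 can be read as narrowing 6.4. The wording is loose and needs aligning.
- *The mechanism becomes uninterpretable.* The change from before inflation to 30 to 90 seconds after leaves little room for slow drift and serves the descriptive objective in section 6.2. Cerebral oximetry, where available, is a further data source in both groups, though not an endpoint. The between-group inference is weakened; the description within the REBOA arm is not lost.

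**Conclusion.** The point holds in this form: as written, the between-group EtCO2 endpoint compares inflation-timed values from REBOA patients who reached inflation with control values that have no corresponding time and no corresponding restriction on who contributes. An observed difference, or the absence of one, could reflect elapsed CPR time or selection rather than occlusion.

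That conclusion rests on the protocol's text and the order of its procedure. Size and direction cannot be derived from the documents; the range of -1.03 to +0.75 kPa depends wholly on the assumed SD, drift, delay and departure pattern. The endpoint is secondary, and the primary ROSC analysis is unaffected. The change should be made, but the trial's main conclusion does not depend on it.

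**What to change.** Define the between-group comparison on time since randomisation:

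- Take EtCO2 at randomisation and at the same prespecified times afterwards in both arms, from the monitor files already collected, where these record EtCO2.
- Analyse by randomised group, with a stated rule for patients who reach ROSC or whose CPR ends before a given time.
- Keep the values before and after inflation as a description within the REBOA arm only.
- Align the wording of sections 6.4 and 12.2 on when control EtCO2 is measured, and carry the same definition into the SAP.

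The cost is some extra extraction from stored files and a change of wording in the protocol, CRF and SAP. Nothing changes for patients. Monitor files may have gaps or may not record EtCO2 in every case, so their completeness by arm should be checked and reported.
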